## Abstract

**Background:**

More than half of patients undergoing paraesophageal hernia repair (PEHR) will have radiographic hernia recurrence at 5 years after surgery. Gastropexy is a relatively low-risk intervention that may decrease recurrence rates, but it has not been studied in a prospective manner. Our study aims to evaluate the effect of anterior gastropexy on recurrence rates after PEHR, compared to no anterior gastropexy.

**Methods:**

This is a two-armed, single-blinded, registry-based, randomized controlled trial comparing anterior gastropexy to no anterior gastropexy in PEHR. Adult patients (≥18 years) with a symptomatic paraesophageal hernia measuring at least 5 cm in height on computed tomography, upper gastrointestinal series, or endoscopy undergoing elective minimally invasive repair are eligible for recruitment. Patients will be blinded to their arm of the trial. All patients will undergo laparoscopic or robotic PEHR, where some operative techniques (crural closure techniques and fundoplication use or avoidance) are left to the discretion of the operating surgeon. During the operation, after closure of the diaphragmatic crura, participants are randomized to receive either no anterior gastropexy (control arm) or anterior gastropexy (treatment arm). Two hundred forty participants will be recruited and followed for 1 year after surgery. The primary outcome is radiographic PEH recurrence at 1 year. Secondary outcomes are symptoms of gastroesophageal reflux disease, dysphagia, odynophagia, gas bloat, regurgitation, chest pain, abdominal pain, nausea, vomiting, postprandial pain, cardiovascular, and pulmonary symptoms as well as patient satisfaction in the immediate postoperative period and at 1-year follow-up. Outcome assessors will be blinded to the patients’ intervention.

**Discussion:**

This randomized controlled trial will examine the effect of anterior gastropexy on radiographic PEH recurrence and patient-reported outcomes. Anterior gastropexy has a theoretical benefit of decreasing PEH recurrence; however, this has not been proven beyond a suggestion of effectiveness in retrospective series. If anterior gastropexy reduces recurrence rates, it would likely become a routine component of surgical PEH management. If it does not reduce PEH recurrence, it will likely be abandoned.

**Trial registration:**

ClinicalTrials.gov NCT04007952. Registered on July 5, 2019.

## Administrative information

Note: the numbers in curly brackets in this protocol refer to SPIRIT checklist item numbers. The order of the items has been modified to group similar items (see http://www.equator-network.org/reporting-guidelines/spirit-2013-statement-defining-standard-protocol-items-for-clinical-trials/).

## Introduction

### Background and rationale {6a}

Paraesophageal hernias occur when the stomach and/or other abdominal organs herniate through the diaphragmatic hiatus into the mediastinum. This abnormal anatomical configuration can lead to symptoms including acid reflux, dysphagia, and shortness of breath, and can also be a risk factor for gastric volvulus, a surgical emergency where blood flow to the stomach may be compromised. For these reasons, the Society of American Gastrointestinal and Endoscopic Surgeons (SAGES) has strongly recommended that all symptomatic paraesophageal hernias be repaired [1]. However, laparoscopic paraesophageal hernia repair (PEHR) presents a challenge for surgeons due to high rates of recurrence. The best available evidence suggests that more than half of patients undergoing laparoscopic PEHR will have radiographic hernia recurrence at 5 years after surgery [2]. Although the likelihood of patients needing revisional surgery for a recurrent hiatal hernia is low, ranging from 0.01 to 7% [2–10], patients with a recurrent hiatal hernia have increased symptoms of heartburn [8, 11–13], early satiety, gas bloat, difficulty and pain with swallowing [3, 4], and worse quality of life [14] compared to those without a recurrence. A prospective study by Le Page et al. evaluating 455 patients over 20 years after PEHR found that recurrences were also associated with increased rates of esophagitis [6]. For these reasons, several methods have been used during PEHR to reduce recurrence rates and improve symptoms. However, there remains substantial variability in techniques utilized, specifically for crural closure, and the use or avoidance of gastropexy, fundoplication, and/or mesh. A significant knowledge gap exists regarding which techniques are the most effective and whether or not they should be tailored for specific patients.

There has been suggestion in the scientific literature that use of anterior gastropexy—in which suture is used to affix the stomach to the anterior abdominal wall—may serve to reduce recurrence rates of PEHR [12, 15]. However, conflicting studies exist [16], and there is no consensus available from the surgical literature, which is limited to small, single-armed series, lacking control arms for comparison. The retrospective nature of this literature, with clear possibilities of selection bias and questionable generalizability, significantly limit a rigorous evaluation of the effect of anterior gastropexy on recurrence rates after laparoscopic PEHR. This leaves many surgeons reluctant to perform anterior gastropexy due to unclear long-term benefits coupled with the potential for short-term pain at the transfascial fixation site.

### Objectives {7}

The primary objective of this trial is to investigate the rates of radiographic PEH recurrence at 1 year in patients receiving anterior gastropexy compared to those receiving no anterior gastropexy during minimally invasive PEHR. The cumulative recurrence rates for laparoscopic PEHR with anterior gastropexy ranges from 0 to 25% [12, 15–20], compared to the recurrence rates without anterior gastropexy ranging from 7 to 66% [3, 16, 21–24]. This data is limited by variable lengths of follow-up and definitions of recurrences. We hypothesize that anterior gastropexy will result in a 15% reduction in PEH recurrence after minimally invasive repair compared to no gastropexy. Based on previously published data and our group consensus, we feel that a 15% reduction is a conservative but clinically important difference that supports the routine use of anterior gastropexy during PEHR.

Secondary objectives include the rates of symptomatic gastroesophageal reflux disease (GERD), dysphagia, odynophagia, gas bloat, regurgitation, chest pain, abdominal pain, nausea, vomiting, postprandial pain, cardiovascular, and pulmonary symptoms as well as patient satisfaction in the immediate postoperative and 1-year follow-up periods between the two groups.

### Trial design {8}

This is a multicenter, single-blinded, registry-based, randomized controlled, parallel group, superiority clinical trial.

## Methods: participants, interventions and outcomes

### Study setting {9}

This is a multicenter study involving two facilities within the Cleveland Clinic Foundation hospital system. The Cleveland Clinic Center for Abdominal Core Health, a center within the Digestive Disease and Surgery Institute (DDSI), at Cleveland Clinic Main Campus in Cleveland, Ohio, is the hosting department for the study. The second facility involved in the study is Cleveland Clinic Fairview Hospital in Cleveland, Ohio.

### Eligibility criteria {10}

The study population includes adult patients (≥ 18 years) undergoing elective, minimally invasive repair of a symptomatic, primary paraesophageal hernia measuring at least 5 cm in height on computed tomography (CT), upper gastrointestinal series (UGI), or endoscopy, where the diaphragmatic crura can be primarily reapproximated at the time of surgery without the use of mesh using either a laparoscopic or robotic approach. Only patients who are able to participate in follow-up and consent to participate will be included. Patients whose operations begin with a minimally invasive approach and are converted to open will be included provided that they meet all other criteria. The technique for crural closure and the use or avoidance of a fundoplication are both left to the discretion of the surgeon.

Exclusion criteria include patients who are not eligible for a minimally invasive repair or have undergone prior esophageal or gastric operations, including hiatal hernia repair, cruroplasty, esophageal lengthening procedures, esophagectomy, or any prior gastric resections. However, patients who have previously undergone gastrostomy tube placement alone will remain eligible for inclusion. Additional exclusion criteria include patients undergoing PEHR with a concurrent bariatric procedure (sleeve gastrectomy, Roux-en-Y gastric bypass, duodenal switch, single-anastomosis gastric bypass, and total gastrectomy), as well as patients undergoing PEHR with concomitant placement of a gastrostomy tube. If the surgeon feels mesh is necessary to augment hiatal closure at the time of operation or if a Collis gastroplasty is required for esophageal length, these patients will also be excluded. Reasons for patient exclusions from the trial will be documented and reported in the Consort diagram.

Surgeon eligibility requires fellowship training with expertise in minimally invasive PEHR. All participating surgeons are also required to undergo training to ensure understanding of the protocol and technical aspects of performing the anterior gastropexy as described in the protocol.

### Who will take informed consent? {26a}

Informed consent will be obtained by the study investigator or co-investigators during the preoperative visit.

### Additional consent provisions for collection and use of participant data and biological specimens {26b}

Not applicable. No additional consent provisions are needed.

#### Interventions

##### Explanation for the choice of comparators {6b}

The effect of anterior gastropexy on recurrence rates and patient-reported symptoms after PEHR is currently unknown, which limits surgeons’ ability to understand the clinical significance of this step. Therefore, anterior gastropexy (intervention arm) will be compared to no anterior gastropexy (control arm) in a prospective, randomized controlled study design.

##### Intervention description {11a}

Key steps of the operation are standardized. Skin preparation, hair removal, perioperative antibiotic administration, and venous thromboembolism prophylaxis are performed per Surgical Care Improvement Project protocol guidelines. Laparoscopic access to the abdomen is obtained by the operating surgeon through either Hasson or optical trocar entry depending on his or her standard practice. Additional laparoscopic ports are placed at the operating surgeon’s discretion to permit liver retraction, working ports, and assistant port(s) for additional retraction. The hernia sac is completely excised from the mediastinum and may be resected from the gastroesophageal junction per the discretion of the surgeon. If necessary for exposure, the short gastric vessels may be divided. The mediastinal esophagus is mobilized to allow for at least 3–4 cm of intraabdominal esophagus. After the surgeon is satisfied with the length and mobility of intraabdominal esophagus, the diaphragmatic crura are reapproximated with permanent suture. If Collis gastroplasty or mesh is deemed necessary, the patient will be excluded from the trial. However, fundoplication may be performed based on surgeon preference and indications, which will be documented.

After crural closure, the patient is randomized to the appropriate treatment arm. Randomization occurs in a 1:1 ratio using a computer-generated random allocation sequence to receive either no anterior gastropexy (control arm) or anterior gastropexy (intervention arm). A study coordinator and/or a research fellow is responsible for the randomization process.

If a patient is randomized to anterior gastropexy (intervention arm), this is performed as the next step of the procedure. Two 2-0 permanent sutures are placed in the midbody of the anterior stomach to provide fixation to the left upper quadrant abdominal wall below the costal margin. Two small incisions are made in the left upper quadrant to allow a suture passer to grasp the remaining ends of the sutures and externalize them from the abdomen at separate fascial punctures. The operation proceeds to the next step per individual surgeon practice. At the time of abdominal desufflation, the sutures are tied which fixates the stomach to the abdominal wall in this position.

After the diaphragmatic crura are reapproximated, if a patient is randomized to the control arm, the operation will proceed to the next step per individual surgeon practice without performing anterior gastropexy. Anterior gastropexy will be the main study intervention that differs between the two groups, which will allow for a direct comparison of patient outcomes attributable to this step.

##### Criteria for discontinuing or modifying allocated interventions {11b}

If at any point during the operation, the surgeon believes inclusion in the study is not in the patient’s best interest, the surgeon may choose to withdraw the patient from the study and complete the operation per his or her standard of care. However, if the patient is included in the study, there will be no deviation from the study protocol and surgeons must perform the key operative steps and technique for anterior gastropexy per the established study protocol. In the event of an immediate recurrence or other postoperative complication, if a gastropexy is added during a subsequent operation, the patient will be included in the intent-to-treat analysis.

As with any surgical procedure, patients may experience pain, bleeding, and discomfort. There is also a small risk of seroma, hematoma, inflammation, wound dehiscence, and infection at the surgical sites. After PEHR, there is a possibility of other symptoms including visceral injury, leak, nausea, vomiting, abdominal distention, dysphagia, odynophagia, GERD, and recurrent hiatal hernia. Patients in both study arms will receive appropriate clinical management for these symptoms at the discretion of the treating surgeon. If at any point during the postoperative period the surgeon believes gastropexy takedown or local suture removal is required to treat an ongoing symptom and/or is in the patient’s best interest, this may be performed at the surgeon’s discretion and will be documented.

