#### Statistical methods

##### Statistical methods for primary and secondary outcomes {20a}

All analyses will be performed using the intent-to-treat population and will be done under the normality assumption, if appropriate. Patient characteristics will be summarized overall and by randomized group, and differences will be described as standardized effects. All tests will be considered significant at 5% level. Outliers for each endpoint will be assessed with a graphical method, such as the box plot. All primary and secondary endpoints will be initially evaluated using all observations and then evaluated with a sensitivity analysis without including points identified as outliers. All statistical analyses will be performed with SAS software (version 9.4; Cary, NA) or R software (version 4.0.0, 2020-04-24; Vienna, Austria).

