### Methods in analysis to handle protocol non-adherence and any statistical methods to handle missing data {20c}

Missing data over time is anticipated to reflect a pattern of “missing at random.” Data collection at the time of the initial surgical consultation (enrolment period) and during the operation (randomization period) will be negligible, as we will ensure capture of all necessary measurements during these time points. If necessary, multiple imputation will be used to impute missing baseline data. Provided that the “missing at random” assumption holds true, multiple imputation of follow-up measurements will not be performed. Since this study involves surgical intervention at the time of randomization, non-adherence to the intervention is not expected to occur.

For missing data during the follow-up period, mixed effect models will be used, which by virtue of their maximum likelihood approach will provide reliable estimates when missing data are “missing at random.” This assumption will be graphically evaluated, and if necessary, sensitivity analyses will be performed to assess the robustness of our findings. This approach will be used for all secondary endpoints.

As for the primary endpoint, obtaining 1-year radiographic assessments will be the most challenging aspect of this study. Several mechanisms are in place to account for missing radiologic data. First, a 20% loss to follow-up rate is expected and was incorporated into the sample size calculation during study development. Second, “intent-to-treat” analysis will be performed, and the “last value carried forward” method will be applied to missing observations. In this method, patients who are lost to follow-up will be considered as “no recurrence,” and the total patient population of 240 will remain as the denominator. Lastly, tipping point analysis will be performed as a sensitivity analysis to examine how missing 1-year radiographic follow-up data affects the validity of our findings.

If non-random missing data patterns are observed, alternate sensitivity analyses, such as pattern mixture models, will be considered.

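### The surgeon's right to withdraw a patient from the study is not limited to the time before randomisation, so it permits exclusion by an unblinded surgeon and is not reconciled with intention to treat

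*Protocol article*

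**What the plan says.** The withdrawal rule is in the protocol article under Criteria for discontinuing or modifying allocated interventions {11b}. Its condition is "If at any point during the operation, the surgeon believes inclusion in the study is not in the patient’s best interest", and its consequence is that "the surgeon may choose to withdraw the patient from the study and complete the operation per his or her standard of care". The next sentence turns to everyone else: "However, if the patient is included in the study, there will be no deviation from the study protocol". The only mention of intention to treat in that section concerns a gastropexy added at a later operation.

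Intervention description {11a} fixes the timing: "After crural closure, the patient is randomized to the appropriate treatment arm". In the gastropexy arm the sutures are placed next, the rest of the operation follows, and then "At the time of abdominal desufflation, the sutures are tied which fixates the stomach to the abdominal wall in this position". Concealment mechanism {16b} has the result passed to the operating room nurse and the surgeon during the operation. Who will be blinded {17a} confirms that the surgeon is not blinded.

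On analysis, section {20a} states "All analyses will be performed using the intent-to-treat population". Section {20c} says that "non-adherence to the intervention is not expected to occur". For the primary endpoint it scores patients lost to follow-up as having no recurrence and keeps 240 as the denominator.

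**The concern.** Part of every operation comes after allocation, with the surgeon aware of the arm, and the withdrawal rule has no time limit that excludes this part. What the rule ends is the patient's place in the study, not only the allocated step. A patient could thus be randomised, have the arm disclosed, and then be removed on a judgement made with that knowledge.

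If removal is related both to the arm and to the patient's risk of recurrence, the arms no longer compare like with like. Analysis cannot repair this if the 1-year imaging was never obtained. The protocol also gives no clear instruction for such a patient: its analysis sections promise intention to treat and foresee no departures, while {11b} creates a route for them.

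**Working it through.** **Design figures.** From Sample size {14}: control recurrence 0.24, reduction of 15% read as 15 percentage points (0.24 against 0.09), two-sided 5% chi-square test, 80% power, 20% loss.

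With pooled variance and no continuity correction, n per arm = [1.96·√(2·0.165·0.835) + 0.8416·√(0.24·0.76 + 0.09·0.91)]² / 0.15² = 94.9, so 95. Then 95/0.80 = 118.75, so 119 per arm and 238 in total, against the stated 240. Power at 96 evaluable per arm (120 × 0.80) is 80.4%. The stated size reproduces, and the point does not depend on it.

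**Sequence.**
1. Dissection, oesophageal mobilisation and crural closure: arm not yet assigned. Withdrawal here is pre-randomisation screening and harmless.
2. Randomisation call: the surgeon learns the arm.
3. Gastropexy sutures or none, remaining steps, desufflation: arm known. The wording of {11b} still allows withdrawal from the study.

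Only step 3 is at issue.

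**Illustration.** The protocol gives no withdrawal rate and no risk for withdrawn patients, so these are assumptions: no true effect, 24% risk in both arms, a fraction w withdrawn from the gastropexy arm only, recurrence risk r among them, and no other losses.

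*If withdrawn patients are dropped*, the remaining risk is (0.24 − w·r)/(1 − w):
- w = 5%, r = 50%: (0.24 − 0.025)/0.95 = 22.6%, a false benefit of 1.4 points.
- w = 10%, r = 50%: (0.24 − 0.05)/0.90 = 21.1%, a false benefit of 2.9 points.
- r from 40% to 80%: 0.8 to 3.0 points at w = 5%, and 1.8 to 6.2 points at w = 10%.
- r = 24%: no shift.

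*If they are treated as lost to follow-up* and scored as no recurrence under {20c}, the arm shows 0.24 − w·r:
- w = 5%, r = 50%: 21.5%, a false benefit of 2.5 points.
- w = 10%, r = 50%: 19.0%, a false benefit of 5.0 points.
- r = 24%: 0.05 × 0.24 = 1.2 points and 0.10 × 0.24 = 2.4 points, so under this scoring the shift does not vanish at average risk.

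*If the withdrawals come from the control arm instead*, the same figures apply with the sign reversed, as a false disadvantage for gastropexy.

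**Power.** Withdrawals of 2%, 5% or 10% in both arms, on top of the 20% loss, lower power from 80.4% to 79.6%, 78.4% or 76.1%. This is minor beside the possible bias.

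**The case against.** The strongest reply is that {11b} never says a withdrawn patient leaves the analysis. Section {20a} puts all analyses on the intention-to-treat population, and a patient withdrawn after allocation and never imaged could fall under the lost-to-follow-up rule, which keeps 240 as the denominator. This stands in part. A reader might infer that the protocol orders these patients out of the analysis, and the text does not go that far. What it supports is that the rule and the analysis sections are not reconciled. The lost-to-follow-up route does not remove the bias either, since it scores these patients as having no recurrence.

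A reader might also infer that the mesh and Collis exclusions can be applied after allocation, because {11a} says: "If Collis gastroplasty or mesh is deemed necessary, the patient will be excluded from the trial". The documents do not support this. In {11a} that decision comes before randomisation, Eligibility criteria {10} treats mesh as part of hiatal closure, and the Discussion says that Collis patients are not randomised. This also means that many of the technically hardest cases have left before the arm is known.

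A third tempting inference is that the gastropexy arm is the more exposed, since it has an extra step. The section on the data monitoring committee {21a} describes gastropexy as optional at the surgeon's discretion, so a surgeon could equally withdraw a worrying control patient in order to add it. Neither direction is established.

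Finally, such withdrawals may be rare, and {10} promises that reasons for exclusion will appear in the CONSORT diagram. That would make removals visible, but it neither keeps the patients in nor requires reporting by arm.

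**Conclusion.** The point holds in this form: the stated rule permits exclusion after randomisation by a surgeon who knows the arm, and it is not reconciled with intention to treat, the denominator of 240 or the expectation of no non-adherence. This is more than detail left to an analysis plan, because the protocol states the withdrawal rule and gives it no time limit.

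The direction of any bias is open and its size unknown. With 5% to 10% withdrawn from one arm at a 50% risk, the distortion would be 1.4 to 2.9 points if they are dropped (at most about a fifth of the 15-point target, 2.9/15) and 2.5 to 5.0 points if they are scored as no recurrence (at most a third, 5.0/15). Those rates, that risk and the one-arm pattern are assumptions. When patients are dropped, there is no distortion if their risk is average.

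**What to change.** Amend {11b} and bring {20a} and {20c} into line with it, on study and analysis status only:
- Surgeon withdrawal from the study applies only before the randomisation call. At the call, confirmation that the patient remains eligible and that the surgeon is content to proceed is logged with the time before the arm is released.
- Every randomised patient stays in the study, is followed to 1-year imaging and is analysed in the allocated arm, whether or not the allocated step was completed. Only the patient's own withdrawal of consent ends follow-up.
- Departures from the allocated step are reported by arm, with number, timing and reason. The statement in {20c} that none are expected is replaced by this rule.

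None of this prescribes operative management; how the operation is completed is outside the point.

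The cost is a one-paragraph amendment and one checklist line at the call, and the protocol reports that recruitment is still open. The downside is slight dilution. If 5% or 10% of the gastropexy arm did not receive the step and kept the control risk, a true 15-point effect would appear as 0.95 × 15 = 14.25 or 0.90 × 15 = 13.5 points.

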### Participant timeline {13}

Estimated patient accrual time is 4 years. Data collection will occur over 1 year from randomization of each patient, which includes the immediate 30-day postoperative and 1-year follow-up periods. Data analysis and manuscript production will occur within 6 months of the completion of data collection (Table 1).

**Table 1 Tab1:** Schedule of enrolment, interventions, and assessments

	Study period			
	Enrolment	Allocation	Post-allocation	Close-out
**Timepoint**	**Preoperative period**	**Intraoperative**	**30-day follow-up**	**1-year follow-up**

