**ASSESSMENTS:**				
**PEH recurrence**				**X**
**GERD**	**X**		**X**	**X**
**Dysphagia**	**X**		**X**	**X**
**Odynophagia**	**X**		**X**	**X**
**Gas bloat**	**X**		**X**	**X**
**Regurgitation**	**X**		**X**	**X**
**Chest pain**	**X**		**X**	**X**
**Abdominal pain**	**X**		**X**	**X**
**Nausea**	**X**		**X**	**X**
**Vomiting**	**X**		**X**	**X**
**Postprandial pain**	**X**		**X**	**X**
**Cardiovascular symptoms**	**X**		**X**	**X**
**Pulmonary symptoms**	**X**		**X**	**X**
**Patient satisfaction**			**X**	**X**
**Demographic data**	**X**			
**Operative details**		**X**		
**Wound morbidity**			**X**	
**Medical morbidity**			**X**	
**Length of stay**			**X**	
**Readmission**			**X**	**X**

*PEH* paraesophageal hernia, *GERD* gastroesophageal reflux disease

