##### Plans to promote participant retention and complete follow-up {18b}

Patients will be scheduled for a postoperative clinic appointment within the 30-day and 1-year follow-up periods, both of which are our routine standard of care. Implementing 1-year radiographic follow-up will be the most challenging aspect of the trial. Several mechanisms have been established to promote patient retention and follow-up completion. The 30-day follow-up period will extend from 15 to 45 days postoperatively, and the 1-year follow-up period will extend from 6 to 18 months postoperatively. Appointment reminders will be sent via patient online portals and nursing phone calls. Virtual follow-up visits can be accommodated and patients can complete UGI or CT scans at their local institutions, provided the imaging can be uploaded into CCF’s digital platform for review. For patients who have missed follow-up appointments, the dedicated study coordinator, research fellow, and/or surgeon will call patients to reschedule or send the GERD-HRQL and numeric rating scales by mail to collect this information. This will increase convenience for patients and protocol adherence. Appropriate statistical analyses will be conducted to account for missing data.

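### Wound and medical morbidity are scheduled at 30 days only, so late suture-site complications and gastropexy takedown have no scheduled 1-year collection and no stated comparison by arm

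*Protocol article*

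**What the plan says.** All references are to the protocol article.

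- **Intervention description {11a}:** "Two 2-0 permanent sutures are placed in the midbody of the anterior stomach to provide fixation to the left upper quadrant abdominal wall". The suture ends are brought out through separate punctures of the fascia and tied.
- **Criteria for discontinuing or modifying allocated interventions {11b}:** the surgeon may act, at any point in the postoperative period, if "gastropexy takedown or local suture removal is required to treat an ongoing symptom". The event is to be documented. No end date is given for that period.
- **Table 1:** the rows "Wound morbidity" and "Medical morbidity" carry a mark in the 30-day column and none in the 1-year column. Readmission is marked at both visits. "Abdominal pain" and the other symptom rows are marked before surgery, at 30 days and at 1 year. There is no row for reoperation, takedown or suture removal.
- **Secondary outcomes, under Outcomes {12}:** wound and medical morbidity are listed among the other variables collected. Clavien-Dindo and the Comprehensive Complication Index will grade complications. No time limit is given for any of these. The numeric rating scales ask about the preceding 7 days.
- **Participant timeline {13}:** "Data collection will occur over 1 year from randomization of each patient".
- **Section 18b:** "The 30-day follow-up period will extend from 15 to 45 days postoperatively, and the 1-year follow-up period will extend from 6 to 18 months postoperatively".

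**The concern.** The events most specific to the randomized step are complications at the fixation site and removal of the fixation. The protocol treats them as relevant to the decision. The background gives pain at the transfascial site as a reason why surgeons hesitate, and the discussion says an ineffective gastropexy may be abandoned partly because of discomfort there. Yet the two morbidity rows in the schedule stop at the 30-day visit, while the efficacy endpoint is read at 1 year.

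Suppose a suture-site infection or painful suture is treated in clinic at month 4. It is not a readmission, and it falls after the only scheduled morbidity entry. If the treatment works, a 7-day symptom scale at 1 year will not show it either. Because the fixation sutures belong to the gastropexy arm, what is lost falls mainly on that arm. The abstract expects gastropexy to become routine if recurrence falls. Readers would then weigh a 1-year benefit against scheduled morbidity data from roughly the first month.

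**Working it through.** **Figures in the plan.** The point rests on no stated figure. The sample size was checked only to confirm that it is untouched. With 0.24 versus 0.09 (the 15% decrease read as percentage points), two-sided alpha 0.05, power 0.80 and a pooled-variance test without continuity correction, 95 per arm are needed. Allowing for 20% loss, 95 / 0.80 = 118.75, so 119 per arm and 238 in total, against 240 stated. With 96 evaluable per arm (120 × 0.80), power is 0.804. Nothing below alters this.

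**Share of follow-up without a scheduled morbidity assessment.** Inputs: the nominal visit at day 30, the last day of its window (day 45, section 18b), and 1 year of data collection taken as 365 days (section 13).

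- From day 45: 1 − 45/365 = 0.877, about 88%.
- From day 30: 1 − 30/365 = 0.918, about 92%.

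This describes the schedule only. It is not an estimate of events missed.

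**What could catch a late fixation-site event, channel by channel:**

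1. *Symptom scales at 1 year.* Abdominal, chest and postprandial pain are scored and the arms compared by mixed models (section 20a). Persistent pain is caught. Pain that has resolved, with or without suture removal, falls outside the 7-day recall. No listed item is specific to the wound or fixation site.
2. *Readmission at 1 year.* This catches events that need a hospital stay, not those managed as an outpatient.
3. *Reoperation in the primary outcome.* It counts at any time in the study, but only for fundoplication disruption, dysfunction or slippage. Takedown of the gastropexy is not on that list.
4. *Documentation under section 11b.* Takedown and suture removal are to be recorded. They appear in no outcome list, no row of Table 1 and no stated comparison.
5. *Adverse event reports (section 22).* They go to the ethics board with no time limit stated, and no comparison by arm is described. There is no data monitoring committee (section 21a).
6. *Complication indices.* No window is stated, and the scheduled morbidity entries are at 30 days only.
7. *Registry (section 19).* Entries are made by surgeons at the point of care, while care outside the institution is allowed (section 11d). Without a scheduled question at 1 year, events treated elsewhere may not be entered.

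Channels 1 and 2 give partial scheduled coverage at 1 year. Channels 3 to 7 do not supply a scheduled, compared record of the remaining events.

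**The case against.** The strongest reply is that much late harm is already collected. Pain, nausea, vomiting, dysphagia and the other symptoms are scored at 1 year and compared by arm. Readmission is marked at 1 year, takedown is documented, and adverse event reporting has no 30-day limit. This stands. A reader might infer from Table 1 that late gastropexy harms in general go uncompared; the documents do not support that. The gap is limited to wound and suture-site complications and other morbidity without readmission, and to takedown or suture removal.

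A reader might also infer from the visit windows that exposure differs threefold between patients (day 15 against day 45, month 6 against month 18). The article never says that counting stops at the visit date, and both arms share the same windows. No bias between arms follows from this. Nor can a number of missed events be given, since no late event rate is stated and some events would be documented anyway.

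A third reply is that the article condenses a fuller protocol, which may hold a takedown field, the windows for the indices and a comparison by arm. That is fair for those details, and their absence alone would not be a finding. It does not remove the main point, because Table 1 sets out the schedule and leaves the 1-year cells of the two morbidity rows empty while filling those of readmission and the symptoms.

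Finally, section 21a holds that efficacy, not safety, is what is uncertain. That explains why late morbidity was given little room. It sits uneasily with section 11b, which expects that some fixations may have to be undone.

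**Conclusion.** The point holds in this limited form and is a cheap improvement, not a flaw in the primary analysis. As scheduled, late wound or suture-site complications without readmission, and takedown or suture removal, have no 1-year collection and no stated comparison by arm. About 88% to 92% of a 365-day follow-up lies after the scheduled morbidity assessment. Any resulting undercount would fall mainly on the gastropexy arm. Its size is unknown.

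This rests on two readings: that Table 1 shows the intended schedule, and that the undefined postoperative period in section 11b can extend past the 30-day visit. If the full protocol already collects and compares these events at 1 year, what remains is to align Table 1 with it. No sample size, power or primary-endpoint figure changes.

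**What to change.** - In Table 1, mark wound morbidity and medical morbidity at 1 year as well as at 30 days.
- Add one row at both visits for gastropexy takedown, suture removal or reoperation, with date and reason. Section 11b already has takedown and suture removal documented.
- Apply Clavien-Dindo and the Comprehensive Complication Index to events up to two fixed limits, 30 days and 1 year after surgery, whatever the visit date.
- State that all of these will be reported by arm.

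The change concerns data collection and reporting only and leaves clinical management as it is. The cost is a little more data entry at a visit that already takes place, plus some registry fields. Recruitment began in June 2019 and the protocol version is dated January 2022, so patients operated on before January 2021 were already past 1 year. For them the items would have to come from retrospective record review. Because outside care is permitted, that review may be incomplete, and the report should say so.
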